# INTERIM AND STATISTICAL ANALYSIS

An interim analysis will be conducted after completion of the 30-day follow up of the first 130 patients, i.e. 50% of the number of patients needed to be enrolled as calculated by power analysis. As comparators will be used patients hospitalized with pneumonia by the SARS-CoV-2 virus in other departments of Greek hospitals in which full data collection is performed by the Hellenic Sepsis Study Group, after written informed consent. Data collection in these departments has been approved by the Ethics Committees of the respective hospitals. For the purpose of this analysis, patients receiving standard-of-care treatment (SOC) will be selected among the total patients whose data are fully collected in order to fulfill the same inclusion and exclusion criteria as patients enrolled in the SAVE trial. Propensity matching will be performed among comparators and 130 patients enrolled in the SAVE trial, so as the 130 comparators will be fully comparable to all below criteria:

- Age
- Comorbidities, as expressed by the Charlson’s Comorbidity Index
- Admission severity scores namely pneumonia severity index (PSI), acute physiology and chronic health evaluation (APACHE) II score, SOFA score and WHO severity classification of COVID-19
- Co-administered treatment, such as azithromycin and dexamethasone

The primary endpoint will expressed as percentage and 95% confidence intervals. Comparisons with historical cases will be done by the Fisher exact test. Any p-value below 0.05 will be considered significant.

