# ADVERSE EVENTS

Adverse events (AEs) and Serious Adverse Events (SAEs) will be collected from baseline until the last patient’s evaluation. Investigators should monitor subjects for adverse events and are responsible for recording ALL adverse events and serious adverse events occurring to a patient during the trial.

An adverse event is any undesirable medical occurrence in a subject administered a pharmaceutical product and which does not necessarily have a causal relationship with this treatment. The time relationship is defined from the moment the AE occurs during therapeutic treatment until 30 days or 5 half-lives after treatment discontinuation. The adverse event may be a sign, a symptom, or an abnormal laboratory finding.

**Serious adverse events** (SAEs) must be reported to within 24 hours. If an adverse event meets any of the following criteria, it is considered SAE:

- **Life-threatening situation** The subject was at risk of death at the time of the adverse event/experience. It does not refer to the hypothetical risk of death if the AE were more severe or were to progress.
- **Inpatient hospitalization** or prolongation of existing hospitalization.
- **Persistent or significant disability/incapacity** Any AE having an outcome that is associated with a substantial disruption of the ability to carry out normal life functions, including the ability to work. This is not intended to include transient interruption of daily activities.
- **Congenital anomaly/birth defects** Any structural abnormality in subject’s offspring that occurs after intrauterine exposure to treatment.
- **Important medical events/experiences** that may not result in death, be life-threatening, or require hospitalization may be considered a serious adverse event/experience when, based upon appropriate medical judgment, **they may jeopardize the subject and may require medical or surgical intervention to prevent one of the outcomes listed above,** i.e., death, a life-threatening adverse event/experience, inpatient hospitalization or prolongation of existing hospitalization, a persistent or significant disability/incapacity, or a congenital anomaly/birth defect. Examples of such medical events/experiences include allergic bronchospasm requiring intensive treatment in an emergency room or at home, blood dyscrasias or convulsions that do not result in inpatient hospitalization, or the development of drug dependency or drug abuse.

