**STATISTICAL ANALYSIS PLAN (5 October 2020)**

The study is powered for the primary endpoint making the hypothesis that 60% of patients with lower respiratory tract infection due to COVID-19 and suPAR≥6 ng/ml upon hospital admission will develop SRF. To decrease this to 45% with power of 90% at a 5% level of significance, two hundred sixty (260) patients need to be enrolled. Taking into consideration, the single-arm study design, 500 patients should be enrolled to make results more robust. Data will be analyzed for the intention-to-treat (ITT) population.

An interim analysis will be conducted after completion of the 30-day follow up of the first 130 patients, i.e. 50% of the number of patients needed to be enrolled as calculated by power analysis. Parallel comparators receiving standard-of-care treatment (SOC) will be used all patients hospitalized at the same time period in eight departments of Internal Medicine in tertiary hospitals of Athens who were participating in the registry of the Hellenic Sepsis Study Group without participating in the SAVE trial ([www.sepsis.gr](http://www.sepsis.gr)). Data and biosample collection is done in the SOC comparators after written informed consent. The same inclusion and exclusion criteria will apply in the parallel comparators under SOC as in patients participating in the SAVE trial. Data collection in these departments has been approved by the Ethics Committees of the participating hospitals. Propensity matching will be performed among comparators to the 130 patients enrolled in the SAVE trial, so as the 130 comparators will be fully comparable to all below criteria:

- Age
- Comorbidities, as expressed by the Charlson’s Comorbidity Index
- Admission severity scores namely pneumonia severity index (PSI), acute physiology and chronic health evaluation (APACHE) II score, SOFA score and WHO severity classification of COVID-19
- Co-administered treatment of azithromycin, hydroxychloroquine and dexamethasone

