Primary outcome and binary secondary outcomes as well as serious adverse event and adverse event rates between the two groups will be expressed as percentages and will be compared by the Fisher exact test, calculating also the respective odds ratios. The time to an event will be compared between the two groups by survival analysis. Stepwise Cox regression analysis will be conducted for the primary outcome and 30-day mortality. Quantitative secondary outcomes will be expressed as median values with respective interquartile range and will be compared by the Mann-Whitney U test.

The cost of hospitalization will be measured by adding the itemized cost of stay, drugs, and interventions and will be expressed as median with respective interquartile range. Salaries of nurse and medical stuff will not be included. Cost comparison will be done by the Mann-Whitney U test.

Qualitative baseline characteristics will be expressed as frequencies and percentages and compared by the Fisher exact test. Quantitative baseline characteristics will be expressed as mean values with standard deviation if following a normal distribution or median values with quartiles if following linear distribution. Comparisons of quantitative baseline characteristics will be done by the Student’s t-test or by the Mann-Whitney U test respectively. Paired comparisons will be done by the Wilcoxon’s rank-signed test. Non-parametric correlations will be done according to Spearman.

Analysis will be conducted with SPSS Version 25.0. All P values will be two-sided. Any P value <0.05 will be considered as statistically significant.

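### The SAP tests AE and SAE rates against registry comparators without stating how, from which day or for how long their events are ascertained, so drug effect and unequal ascertainment cannot be separated

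*Supplement*

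**What the plan says.** The SAP plans, for the SAVE and standard-of-care groups, that "serious adverse event and adverse event rates between the two groups will be expressed as percentages and will be compared by the Fisher exact test", with odds ratios. It adds that "All P values will be two-sided" and "Any P value <0.05 will be considered as statistically significant". It places no restriction on which events are compared and plans no sensitivity analysis for how they were found.

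For SAVE patients, protocol v3.0 lists AE and SAE recording at every visit on days 1 to 10 and on day 14 (Patients' visits and interventions; Appendix II). After discharge these visits may be held by phone or internet. The Adverse Events section makes investigators responsible for recording all events. It sets the window as follows: "The time relationship is defined from the moment the AE occurs during therapeutic treatment until 30 days or 5 half-lives after treatment discontinuation".

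The protocol takes the comparators from "other departments of Greek hospitals in which full data collection is performed by the Hellenic Sepsis Study Group". The SAP describes them as patients "who were participating in the registry of the Hellenic Sepsis Study Group without participating in the SAVE trial". Both texts mention consent, ethics approval and the same eligibility criteria. Neither gives an AE collection schedule, a day from which events count, or a period over which they count.

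**The concern.** A comparison of event rates is interpretable only if events are looked for in the same way and over the same time in both groups. Here ascertainment is specified for one group only. If the registry finds fewer of the events that occur, anakinra looks harmful when it is not. If SAVE events are counted over a shorter period, anakinra looks safer than it is. The matching variables (age, Charlson index, severity scores, co-administered drugs) address baseline risk. They do nothing about an outcome detected differently in the two groups. What is at stake is a safety statement with a P value and an odds ratio that readers would attribute to the drug.

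**Working it through.** **What is specified for each group**

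| Item | SAVE patients | Registry comparators |
| --- | --- | --- |
| AE/SAE recording schedule | Days 1-10 and 14 | Not stated |
| Duty to record all events | Yes (Adverse Events) | Not stated |
| Contact after discharge | Phone or internet visit | Not stated |
| Start of observation | Baseline | No index day stated |
| End of observation | Scheduled recording ends on day 14; the window runs 30 days or 5 half-lives after stopping | No stopping date exists for a drug they do not receive; none substituted |

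The SAVE window is itself unsettled. With the last scheduled dose on day 10, 30 days after stopping is day 10 + 30 = day 40, while scheduled recording stops on day 14.

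**Inputs for the illustration.** The documents give the sample size ("An interim analysis will be conducted after completion of the 30-day follow up of the first 130 patients"; 130 matched comparators, "so as the 130 comparators will be fully comparable to all below criteria"), Fisher's exact test, and two-sided P<0.05. They give no AE or SAE rate, so there is no figure of the plan's own to reproduce. Assumed: the same true risk t in both groups (20% to 80%), complete capture in SAVE, and a registry that captures a share c of patients with an event (50% to 100%).

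**Formula.** The observed SAVE rate is t and the observed comparator rate is t × c. The chance of a significant result is the sum, over all pairs of counts (a, b) with Fisher P<0.05, of Bin(a; 130, t) × Bin(b; 130, t × c). This is exact enumeration. The spurious odds ratio is [t/(1−t)] / [tc/(1−tc)]. For example, t = 0.40 and c = 0.70 give tc = 0.28 and (0.40/0.60)/(0.28/0.72) = 1.71.

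**Chance of a significant difference, either direction, with no drug effect**

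| True risk | c = 100% | 90% | 80% | 70% | 50% |
| --- | --- | --- | --- | --- | --- |
| 20% | 3.6% | 5.1% | 10.3% | 20.3% | 56.0% |
| 40% | 3.6% | 7.9% | 22.5% | 48.2% | 93.0% |
| 60% | 3.6% | 13.8% | 45.6% | 80.8% | 99.8% |
| 80% | 3.6% | 27.9% | 78.9% | 98.4% | 100% |

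When c is below 100%, nearly all of these results are in the direction of SAVE higher. The spurious odds ratio runs from 1.14 (t = 20%, c = 90%) to 6.00 (t = 80%, c = 50%).

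**Window mismatch, with equal capture.** Assume a 30-day risk of 30% in both groups and a constant hazard: λ = −ln(1 − 0.30)/30 = 0.01189 per day.

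- SAVE counted to day 14, comparators to day 30: the SAVE rate is 1 − exp(−14λ) = 15.3% against 30%. A significant result arises in about 78% of trials, almost always SAVE lower.
- SAVE counted to day 40, comparators to day 30: the SAVE rate is 1 − exp(−40λ) = 37.8% against 30%. A significant SAVE-higher result arises in about 23%.

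The choice of window, which the plan leaves open, is enough to reverse the direction.

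**The case against.** Several counter-arguments have force.

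- A reader might infer that the protocol's AE definition cannot apply to comparators at all. The documents do not support this. The definition refers to a pharmaceutical product in general, and comparators receive drugs; three of them are matching variables in the SAP. The seriousness criteria need no study drug either. Only the window lacks an anchor, and an index day would supply one.
- A reader might infer that the registry under-records events, so that the comparison measures surveillance rather than the drug. The documents are silent on registry AE capture. What they do say, including full data collection, suggests structured recording. That general phrase does not establish equivalent AE ascertainment, but silence is not evidence of poor capture.
- A reader might suppose that SAVE investigators would leave out expected drug effects. The duty to record all events contradicts this, and relatedness is assessed separately.
- Serious events may be found more evenly than minor ones. At a 20% risk and 90% capture the excess of false findings is small: 5.1% against 3.6%.
- AE rates are not among the listed endpoints, and under-capture in the registry would count against anakinra rather than for it. This limits the consequence. A shorter SAVE window, however, would favour anakinra.

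These points narrow the claim. They leave untouched that the plan tests an outcome whose ascertainment and window are specified in one group only.

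**Conclusion.** The point holds as a gap in specification that makes the planned test uninterpretable as it stands. Followed as written, it mixes drug effect with any difference in how and for how long events were sought, and matching on baseline factors cannot undo that.

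The size is unknown. Over the assumed 90% to 50% capture, false significance runs from about 5% to 56% at a 20% true risk, 8% to 93% at 40% and 14% to 99.8% at 60%, against about 4% with equal capture. A 14-day against 30-day window gives about 78% in the other direction. All of these rest on assumed risks, assumed capture shares and, for the window, a constant hazard. They show that modest differences can matter, and are no estimate of what this registry does. The change is worth making, but safety is not the primary endpoint and the primary analysis does not depend on it.

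**What to change.** In the SAP's paragraph on outcome comparisons:

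1. Define an index day for both groups, for example the first study-drug day in SAVE and the corresponding hospital day in the matched comparator, and one common fixed window from that day.
2. State the comparators' AE definition, source and frequency of collection.
3. Limit between-group tests and odds ratios to death and to serious events obtained in the same way in both groups from hospital records.
4. Include laboratory-defined events only if testing is shown to be comparably available in both groups. SAVE blood counts and biochemistry are recorded only when available, so these events could carry the same problem.
5. Report all other AEs and SAEs for SAVE descriptively, without a P value against the registry.

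The cost is SAP wording plus record abstraction for up to 130 + 130 = 260 patients at the planned comparison. There would be no P value for overall AE rates.

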## Study drug

The active study drug i.e. anakinra will be provided in the form of pre-filled ready-to-use syringes. All syringes need to be stored at 2-8°C at the study site at a refrigerator with recording of temperature. In case recording indicates deviation of temperature below 0°C or above 10°C for more than a day, stored syringes need to be replaced by the Sponsor. At the exterior of each syringe there will be a letter and a 4-digit number. The letter refers to the study site, the first two digits of the number refer to the serial number of enrolled patient at the respective study site and the last two digits refer to the day of treatment. For example, the code A0102 refers to study site A, patient number 01 at that study site and treatment day 2. In case of patients discharged earlier and continuing the drug by self-injection, pre-filled syringes will be provided in a cooling bag.

The adverse events of anakinra are classified as very common (≥ 1/10), common (≥ 1/100 to < 1/10) and uncommon (≥ 1/1,000 to < 1/100) and they are presented in the Table below^7^:

| **MedDRA Organ System** | **Frequency** | **Undesirable Effect** |
| --- | --- | --- |
| Infections and infestations | Common | Serious infections |
| Blood and lymphatic system disorders | Common | Neutropenia  Thrombocytopenia |
| Immune system disorders | Uncommon | Allergic reactions including anaphylactic reactions, angioedema, urticaria and pruritus |
| Nervous system disorders | Very common | Headache |
| Hepatobiliary disorders | Uncommon | Hepatic enzyme increased |
|  | Not known | Non-infectious hepatitis |
| Skin and subcutaneous tissue disorders | Very common | Injection site reaction |
|  | Uncommon | Rash |
| Laboratory | Very common | Blood cholesterol increased |

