# STUDY ENDPOINTS

## Primary study endpoint

The primary study endpoint is the rate of patients who will develop SRF (see Appendix V for definition) until day 14. Patients dying before study visit of day 14 are considered achieving the primary endpoint.

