# APPENDIX V Definition of severe respiratory failure

Presence of all of the following:

- pO_2_/FiO_2_ less than 150
- Need for mechanical or non-mechanical ventilation (CPAP)

**suPAR-GUIDED ANAKINRA TREATMENT FOR VALIDATION OF THE RISK AND EARLY MANAGEMENT OF SEVERE RESPIRATORY FAILURE BY COVID-19: THE SAVE OPEN-LABEL, NON-RANDOMIZED SINGLE-ARM TRIAL**

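### SRF meets the protocol's SAE definition and nothing exempts it, so the planned SAE comparison would be dominated by the primary endpoint and can mask an excess of other serious events

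*Supplement*

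**What the plan says.** The Adverse Events section of protocol version 3.0 sets a wide net: "An adverse event is any undesirable medical occurrence in a subject administered a pharmaceutical product", with no causal link required. Investigators are "responsible for recording ALL adverse events and serious adverse events occurring to a patient during the trial". An event is serious if, among other criteria, it is life-threatening, explained as "The subject was at risk of death at the time of the adverse event/experience", or if it leads to or lengthens a hospital stay.

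The primary endpoint section reads: "The primary study endpoint is the rate of patients who will develop SRF (see Appendix V for definition) until day 14". Appendix V defines SRF as a pO2/FiO2 ratio below 150 together with a need for CPAP or mechanical ventilation. Patients who already have it are excluded at entry, so every SRF is a new event.

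For the analysis, the SAP's paragraph on outcome comparisons states, for SAVE patients against matched standard-of-care comparators: "serious adverse event and adverse event rates between the two groups will be expressed as percentages and will be compared by the Fisher exact test". The same sentence covers the primary outcome.

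The table of undesirable effects in the Study Drug section has the row "Infections and infestations | Common | Serious infections". The protocol defines common as at least 1 in 100 and below 1 in 10.

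**The concern.** A patient whose oxygenation falls below the Appendix V threshold and who needs ventilatory support meets the life-threatening criterion and normally the hospitalisation criterion too. Neither the protocol nor the SAP says that endpoint events or disease progression are left out of SAE recording, and no SAE analysis without SRF is planned. SRF therefore enters the rate that the SAP tests.

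SRF is expected in a third to more than half of patients, while the serious drug risk that the protocol names is in the 1-10% band. If anakinra works, the SAE rate falls because SRF falls, whatever happens to other serious events. The comparison would then repeat the efficacy result under a safety label, and a lower SAE rate could be read as reassurance that the data do not give.

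**Working it through.** **Inputs from the documents.** SRF 55% v 35% (protocol, Number of Patients) or 60% v 45% (SAP); 130 v 130 matched patients, the only comparison size that the SAP specifies; two-sided Fisher test at 0.05.

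**Assumed.** The rate q of SAEs other than SRF in comparators, doubling to 2q on anakinra. The documents give no value, so a range is shown.

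**The plan's own figure.** For two proportions, n per group = [1.960·√(2p̄(1−p̄)) + 1.282·√(p1(1−p1)+p2(1−p2))]² / (p1−p2)².
- 55% v 35%: 128 per group, 256 in total, consistent with the stated 260.
- 60% v 45%: 231 per group, 462 in total, so 260 is not reproduced.

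That mismatch is a separate matter. Both pairs of rates are carried through below.

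**Any-SAE rate.** With SRF counted and other SAEs independent of it, P(any SAE) = 1 − (1 − p_SRF)(1 − q). Example with protocol rates and 5% v 10%: comparators 1 − 0.45×0.95 = 57.3%; anakinra 1 − 0.65×0.90 = 41.5%.

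The last three columns are exact Fisher rejection probabilities at 130 v 130.

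| Other SAEs, comparator v anakinra | SRF rates | Any SAE | OR | Significant for anakinra | Significant against | Test without SRF flags harm |
| --- | --- | --- | --- | --- | --- | --- |
| 2% v 4% | protocol | 55.9% v 37.6% | 0.48 | 82% | <0.1% | 7% |
| 2% v 4% | SAP | 60.8% v 47.2% | 0.58 | 56% | <0.1% | 7% |
| 5% v 10% | protocol | 57.3% v 41.5% | 0.53 | 69% | <0.1% | 25% |
| 5% v 10% | SAP | 62.0% v 50.5% | 0.63 | 42% | <0.1% | 25% |
| 10% v 20% | protocol | 59.5% v 48.0% | 0.63 | 42% | <0.1% | 56% |
| 10% v 20% | SAP | 64.0% v 56.0% | 0.72 | 22% | <0.1% | 56% |
| 20% v 40% | protocol | 64.0% v 61.0% | 0.88 | 5.5% | 0.5% | 93% |
| 20% v 40% | SAP | 68.0% v 67.0% | 0.96 | 2.8% | 1.2% | 93% |
| 25% v 50% | protocol | 66.3% v 67.5% | 1.06 | 1.1% | 3.0% | 98% |
| 25% v 50% | SAP | 70.0% v 72.5% | 1.13 | 0.6% | 4.9% | 98% |

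**Share of SRF.** At 10% v 20%, patients with SRF are 0.55/0.595 = 92% of comparators and 0.35/0.48 = 73% of anakinra patients with any SAE (protocol rates), or 0.60/0.64 = 94% and 0.45/0.56 = 80% (SAP rates).

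**Break-even.** Setting (1−p1)(1−q) = (1−p2)(1−2q) gives q = (p1−p2)/[2(1−p2) − (1−p1)].
- SAP rates: 0.15/0.70 = 21.4%.
- Protocol rates: 0.20/0.85 = 23.5%.

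Below this, a doubling still leaves the SAE point estimate in favour of anakinra.

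**Dependence on independence.** If other SAEs occur only in patients without SRF, the rates add and break-even is q = p1 − p2, that is 15% (SAP) or 20% (protocol). If they occur only in patients with SRF, the SAE comparison is identical to the SRF comparison.

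**If SRF rates are equal.** The difference in other SAEs is multiplied by (1 − p_SRF). With 55% in both groups and 10% v 20%, any SAE is 59.5% v 64.0%: a gap of 4.5 points instead of 10. The signal is diluted, not reversed.

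**The case against.** No sentence calls SRF an SAE. The visit lists and the Appendix II schedule record SRF and AE/SAE on separate lines, so a site might treat SRF as captured already and not report it again. It is fair to say that SRF's status is inferred from the definitions. But separate lines do not take SRF out of the SAE count when all events are to be recorded and none is exempted. If sites read the rule differently, or if the registry departments that supply comparators apply another one, the comparison is harder still to interpret. Neither document describes how SAEs are recorded in comparators.

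The SAP also does not name an overall SAE rate as the main safety test. Its plural wording could allow rates by event type, which would show serious infections. That stands as far as it goes: the level of tabulation is unspecified, and no breakdown is promised.

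A reader might infer that the plan will usually produce a significant but false safety advantage. The figures do not support that. At 10% v 20% a significant result in favour of anakinra comes in 22-42% of trials, so non-significance is the more common outcome, and above break-even the estimate turns against anakinra. A reader might also infer that the SAE test fails whether or not the drug works. With equal SRF rates it only loses sensitivity.

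Finally, leaving SRF out does not isolate drug harm. Complications that follow SRF stay in the remaining count and would fall if SRF falls. The test without SRF also has little power when other events are rare (7% at 2% v 4%).

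**Conclusion.** The point holds as a gap in the safety analysis, not as an error in the primary analysis. Read plainly, the definitions put SRF into the SAE rate. At the plan's own SRF rates, that rate then largely restates efficacy and can hide or reverse a doubling of other serious events while their comparator rate is below about 21-24% (15-20% if they occur only in patients without SRF). For 5% v 10% and 10% v 20%, the SAE test is significant against anakinra in under 0.1% of trials, while a test without SRF flags harm in 25% and 56%.

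The size rests on three assumptions: a rate of other SAEs that the documents do not give, independence from SRF, and a real reduction in SRF. The documents do not support the stronger statement that they expressly require SRF to be counted as an SAE, nor that a significant finding of fewer SAEs is to be expected.

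**What to change.** In the SAP's paragraph on outcome comparisons, add the proportion of patients with at least one SAE other than SRF as defined in Appendix V, compared in the same way and shown alongside the all-SAE rate. Apply one rule to SAVE patients and comparators. Give serious infections their own line. State that the all-SAE rate alone will not be interpreted as evidence of safety.

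In the protocol's Adverse Events section, say whether SRF is reported as an SAE and have SRF events flagged in the SAE record. Show deaths by whether SRF had been recorded by day 14, without attributing cause. SRF is recorded only to day 14, whereas the AE window runs to 30 days or 5 half-lives after treatment and mortality is followed to day 90, so later deaths cannot be classed by SRF from that record.

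The cost is one table and one flag, with no added patients or visits; SRF must be established in both groups for the primary comparison anyway. The report should state as a limitation that complications following SRF remain in the count without SRF.

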## Study population

Patients who meet ALL the following inclusion criteria and who do not meet any of the following exclusion criteria are allowed to be enrolled:

Inclusion criteria

1. Age equal to or above 18 years
2. Male or female gender
3. In case of women, unwillingness to remain pregnant during the study period.
4. Written informed consent provided by the patient or by one first-degree relative/spouse in case of patients unable to consent
5. Confirmed infection by SARS-CoV-2 virus
6. Findings in chest-X-ray or in chest computed tomography compatible with lower respiratory tract infection
7. Plasma suPAR ≥6ng/ml

Exclusion criteria

- Age below 18 years
- Denial for written informed consent
- Any stage IV malignancy
- Any do not resuscitate decision
- Presence of respiratory failure as defined in Appendix V
- Αny pO_2_/FiO_2_ ratio less than 150
- Any need for CPAP or mechanical ventilation
- Any primary immunodeficiency
- Less than 1,500 neutrophils/mm^3^
- Known hypersensitivity to anakinra
- Oral or IV intake of corticosteroids at a daily dose equal or greater than 0.4 mg prednisone for a period greater than the last 15 days.
- Any anti-cytokine biological treatment the last one month
- Severe hepatic failure
- Severe renal failure
- Pregnancy or lactation. Women of child-bearing potential will be screened by a urine pregnancy test before inclusion in the study

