# APPENDIX III The SOFA score

| **Variable** | **0 points** | **1 point** | **2 points** | **3 points** | **4 points** |
| --- | --- | --- | --- | --- | --- |
| PaO_2_/FiO_2_(mmHg) | ≥400 | <400 | <300 | <200 | <100 |
| Platelets (per mm^3^) | ≥150 | <150 | <100 | <50 | <20 |
| Hypotension | MAP≥ 70 mmHg | MAP<70 mmHg | Dobutamine whatever dose | Adrenaline≤0.1* or  Noradrenaline  ≤0.1* | Adrenaline>0.1* or  Noradrenaline >0.1* |
| Glasgow Coma Scale | 15 | 13-14 | 10-12 | 6-9 | <6 |
| Bilirubin (mg/dl) | <1.2 | 1.2-1.9 | 2.0-5.9 | 6.0-11.9 | ≥12 |
| Creatinine (mg/dl) or Urine output | <1.2 | 1.2-1.9 | 2.0-3.4 | 35-4.9 or <500ml/day | ≥5.0 or  <200ml/day |

*μg/kg/min

Each variable is scored between 0 and 4. The SOFA score is the sum of the score of each variable

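### The between-group SRF comparison controls baseline pO2/FiO2 only partly: the Fisher test and odds ratio are unadjusted, and neither the matching nor the stepwise Cox model guarantees oxygenation balance

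*Supplement*

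**What the plan says.** **Endpoint.** Protocol v3.0, Appendix V, defines SRF by "Presence of all of the following": "pO_2_/FiO_2_ less than 150", and need for mechanical ventilation or CPAP. The primary endpoint section adds: "Patients dying before study visit of day 14 are considered achieving the primary endpoint".

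**Comparison.** The SAP of 5 October 2020 states that the primary outcome and binary secondary outcomes in the two groups "will be compared by the Fisher exact test, calculating also the respective odds ratios". Two sentences later it adds: "Stepwise Cox regression analysis will be conducted for the primary outcome and 30-day mortality". It names no covariates for that model.

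**Baseline control.** The exclusion criteria rule out any "pO_2_/FiO_2_ ratio less than 150", and the SAP applies the same criteria to the comparators. In the paragraph on the interim analysis, 130 comparators are propensity matched to 130 SAVE patients. The matching variables are age, Charlson index, PSI, APACHE II, SOFA, WHO class and co-treatments. pO2/FiO2 itself is not on that list. In Appendix III it enters SOFA in five bands, "≥400 | <400 | <300 | <200 | <100", as one of six summed items.

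**The concern.** The comparators are registry patients who were not randomised, so starting oxygenation may differ systematically as well as by chance. Baseline pO2/FiO2 is the starting value of one component of the endpoint, so patients who start close to 150 have less far to fall. If the treated group starts better oxygenated than its matched comparators, some of the difference in SRF would be credited to anakinra. If it starts worse, a benefit would be understated.

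Fisher's test cannot correct for such a gap. Its odds ratio would carry it, and a reader of a positive result could ask whether the treated patients simply began with better lungs. The plan as written has no set answer to that question.

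**Working it through.** **1. The plan's own figure.** Pooled two-proportion formula, two-sided 5%, 90% power:

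n per group = [1.96·√(2p̄q̄) + 1.2816·√(p1q1 + p2q2)]² / (p1 − p2)²

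- Protocol v3.0, 55% v 35%: [1.96·√0.495 + 1.2816·√0.475]² / 0.20² = 128 per group, 256 in total. The stated 260 reproduces within 3%.
- SAP, 60% v 45%: [1.96·√0.49875 + 1.2816·√0.4875]² / 0.15² = 231 per group, 462 in total. The stated 260 does not reproduce.

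With 130 per group, the unadjusted large-sample power is 90.5% at the protocol rates and 68.0% at the SAP rates. Exact Fisher power is 88.6% and 64.8%. The two sets of rates for one N are a separate matter to reconcile; both are used below.

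**2. Does matching on totals balance pO2/FiO2?** By Appendix III, eligible patients score 3 points (150-199), 2 (200-299), 1 (300-399) or 0 (400 and above). Patients at 205 and 295 score the same on the item. A patient at 155 with no other points and one at 390 with two points from other organs both total 3.

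An illustration, with assumed inputs: log-normal pO2/FiO2 cut at 150.
- Median 250 or 300, log SD 0.35, other-organ points Poisson with mean 0.3-1.2: total SOFA explains 41-68% of the variance of log pO2/FiO2.
- Median about 260, Poisson mean 0.3-1.5: exact matching on total SOFA leaves about 30-70% of a raw gap, so 0.5 SD becomes 0.15-0.32 SD.

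PSI, APACHE II and WHO class may shrink this further; that was not modelled.

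**3. What a residual gap does when the drug does nothing.** With slope β (log-odds of SRF per SD of baseline pO2/FiO2) and gap δ SD in favour of the treated, the crude log odds ratio is about −βδ. For δ = 0.2 and β = 0.5, 1.0, 1.5 this gives odds ratios of exp(−0.1) = 0.90, exp(−0.2) = 0.82 and exp(−0.3) = 0.74. Simulated averages are 0.90-0.91, 0.84-0.85 and 0.80; the approximation overstates the shift when the slope is steep.

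Rejection rates with no drug effect, SRF 55%, 130 v 130, 1,000 runs per setting:

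| β (correlation with SRF) | Fisher, 0.2 SD | Adjusted, 0.2 SD | Fisher, 0.3 SD | Adjusted, 0.3 SD |
| --- | --- | --- | --- | --- |
| 0.5 (−0.23) | 5.5% | 4.9% | 6.6% | 4.3% |
| 1.0 (−0.41) | 7.5% | 4.4% | 16.7% | 3.7% |
| 1.3 (−0.49) | 11.9% | 6.4% | 19.6% | 4.7% |

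Adjusted means a logistic model with group and continuous baseline pO2/FiO2. At a gap of 0.4 SD and β of 0.5-1.5, Fisher rejects in 9-39% of runs and the adjusted model in 4-6%.

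**4. Power with no gap, SAP rates.**

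| β | Fisher | Unadjusted, large-sample | Adjusted | Gain from adjustment |
| --- | --- | --- | --- | --- |
| 0.5 | 64.8% | 68.0% | 70.5% | 70.5 − 68.0 = 2.5 points |
| 1.0 | 62.7% | 68.0% | 73.7% | 73.7 − 68.0 = 5.7 points |
| 1.3 | 62.4% | 68.0% | 77.3% | 77.3 − 68.0 = 9.3 points |

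The rest of the distance to Fisher is that test's conservatism. At the protocol rates, adjusted power is 91.7%, 94.3% and 95.5% against 90.5%, a gain of 1.2, 3.8 and 5.0 points. A steeper β of 1.5 gives 83% at the SAP rates, so the gain depends on the assumed slope. None of these runs includes matching, which would use up part of the covariate's prognostic value.

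**The case against.** The strongest reply is that the plan does not disregard oxygenation. Both groups share the exclusion below 150, four severity measures enter the propensity model, and a multivariable Cox model is planned for the primary outcome. All three are real controls, and it would be wrong to say that the plan ignores baseline pO2/FiO2. They do not close the gap, however. The exclusion only truncates the range, the totals blur the value, and a stepwise model with no stated candidates may never include it or may drop it.

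The pair at 155 and 390 is an extreme case. It needs two offsetting points from other organs, and the exclusion of severe renal and hepatic failure makes such points less common. The pair at 205 and 295 needs none.

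Scope also matters. The 130 v 130 comparison is the interim analysis. Protocol v3.0 lists the comparison with comparators as a secondary endpoint; the primary endpoint is a rate, reported with its 95% confidence interval. The figures above apply to that interim comparison.

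Two stronger readings are tempting.
- A reader might infer that a baseline gap exists. The documents show no such gap and give neither its size nor its direction.
- A reader might infer that adjustment narrows the interval for the odds ratio. It does not. In simulation at the SAP rates, the standard error of the log odds ratio rises from 0.252 to 0.262, 0.282 and 0.297 at β = 0.5, 1.0 and 1.3. Power rises because the conditional odds ratio lies further from 1. It is a different quantity from the crude one.

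**Conclusion.** The concern holds in limited form. The comparison of SRF, with death counted as an event, is unadjusted in a non-randomised setting, and the planned controls do not guarantee balance in the starting value of an endpoint component.

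Bias is the main issue. A residual gap of 0.2-0.3 SD in favour of the treated would raise Fisher's false-positive rate from 5% to about 6-20%; adjustment holds it at 4-6%. At the weak end of the assumed range the excess is negligible. Power is secondary: roughly 2-9 points at the SAP rates, and less if matching has already removed part of the variation.

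These sizes rest on two assumptions that the documents cannot settle: how strongly baseline pO2/FiO2 predicts SRF (correlation 0.23-0.49), and how large a gap survives matching. The SAP should be changed because the change is cheap and answers an obvious challenge to any positive result.

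**What to change.** 1. Add continuous baseline pO2/FiO2 to the propensity model and report its standardised difference after matching.
2. Make the main between-group analysis of SRF a pre-specified logistic model with group and baseline pO2/FiO2 (continuous, log scale), both always kept. Report a standardised risk difference with 95% CI, label the odds ratio as conditional, and keep Fisher with the crude odds ratio as supportive.
3. Force the same covariate into the Cox model and list that model's other covariates in advance.

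This is SAP wording only, with no new patients or visits: eligibility and SOFA already call for the value in both groups. There are two small costs. The SAP must state which day supplies the baseline value: for SAVE patients this would be the start of treatment, while the comparators' corresponding day is not defined. Estimated rather than measured pO2/FiO2 values need a flag.
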